#### Quantitative analysis

Multivariate analysis of variance (MANOVA) will be used to examine differences in the primary and secondary outcome measures between the intervention and matched control groups. Within-groups differences will be measured at each time-point, including baseline. Baseline scores will be included as a covariate to allow for regression to the mean and a multiple regression model will be used. A step-wise method of regression analysis will be conducted with predictors entered using the backward method. This method will be used for exploratory model building and will be cross-validated by then randomly splitting the data. The dependent variables of interest will be strategies used to cope with pain and pain knowledge. The reliability of the Pain Coping Strategies Questionnaire and the Pain Coping Scenarios Questionnaire will be assessed by Cronbach’s alpha and validity will be assessed by correlating the measures against one other. Predictors will include the demographic characteristics of age and degree of intellectual disability as well as time since onset of menstruation; frequency and duration of menstruation; number and frequency of menstrual symptoms experienced and history, treatment and use of medication to manage gynaecological problems and other medical conditions.

Process evaluation will be conducted to assess change over time for the primary outcome measures. This will be done by looking at within groups differences at each of the assessment time points. To assist with process evaluation, sessions 2 – 5 focused on behavioural coping strategies and sessions 7 – 10 were dedicated to cognitive coping strategies.

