### Study aims & objectives

This pilot study aimed to evaluate if a theory-based cognitive-behavioural therapy programme for menstrual pain management (derived from the *Feeling Better* manual) is more effective than usual care in helping young women with intellectual disabilities to manage their menstrual pain. In order to answer this question, a small non-randomised controlled trial was conducted comparing the use of menstrual pain management programme with usual care in an intellectual disability service in the west of Ireland. The study included a number of potential secondary outcome measures in addition to the primary outcome measures of pain coping strategies used and pain knowledge. It will enable us to determine if:

1. Participation in the menstrual pain management group results in an increase in participants’ ratings of pain coping strategies, pain management knowledge and pain self-efficacy and if this is maintained at 3 month follow-up.

2. Participation in the menstrual pain management group results in a reduction in self-ratings of pain intensity and pain interference by participants and reduced ratings of pain intensity and pain interference amongst participants, as rated by their parents, and if these reductions are maintained at 3 month follow-up.

3. Participants whose parents score highly on pain-catastrophizing experience greater pain intensity and greater pain interference with quality of life. Catastrophizing – experiencing extremely negative thoughts about one’s plight and interpreting even minor problems as major catastrophes – appears to be a powerful way of thinking that greatly influences pain and disability and is important in determining one’s reaction to pain [22]. Goubert, Eccleston, Vervoort, Jordan and Crombez [23] found that parents’ catastrophic thinking about their child’s pain had a significant contribution in explaining the child’s disability and school attendance. For this reason, parental catastrophizing is expected to affect participants’ ratings of pain intensity, pain interference and pain coping strategies used.

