Participants rated pain intensity during their last menstrual period using a coloured Visual Analogue Scale (VAS) [31]. On this scale, 0 = no pain and 10 = lots of pain. Due to the challenges associated with using numerical rating scales with individuals with intellectual disabilities, proxy measures of pain severity were also obtained from the parents of participants. Pain interference was measured by a modified version of the Brief Pain Inventory – Short Form [32]. This questionnaire used a likert scale where 0 = did not interfere and 10 = completely interferes. The modified version of the Brief Pain Inventory – Short Form used in this study was specifically generated for the purpose of this research project. The specific modifications required included front and back female body outlines to enable participants to identify the areas of the body in which they experienced menstrual pain, omission of some questions e.g. questions regarding pain in the last 24 hours (participants may not be menstruating at the time of administration of questionnaires), changes to the questions on categories assessed (wording changes and additional categories included) and modifications to the response categories by including the use of a visual analogue rating scale in conjunction with a numerical rating scale. Modifications to the original Brief Pain Inventory – Short Form were required to enable it to be understood by and used with people with intellectual disabilities as well as to make it relevant to the assessment of menstrual pain, which is an intermittent rather than a constant type of pain.

Secondary outcome measures were administered to participants at T1: baseline (pre-intervention), T4:12 weeks from baseline (post-intervention) and T5: 3 months follow-up. Secondary outcome measures were administered to parents/guardians at T1, T4 and T5. The VAS was also administered to participants at T2: 5 weeks from baseline and T3: 10 weeks from baseline to determine the impact of the intervention on pain severity, over time.

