### Data analyses

#### Sample size and power calculation

There are a lack of well-conducted controlled trials and a lack of information about effect sizes of CBT with people with an intellectual disability within published research in this area. The authors were reliant on the few previous studies available regarding this area of research and for this reason, the feasibility study by Hassiotis et al. [35] was used as a guideline in calculating sample size requirement. This study proposed a total sample of 30 to be allocated across two conditions although there is currently discussion that feasibility trials ought to include up to 60 individuals. We based our sample size on the Hassiotis paper and allowed for 20% attrition, thus we recruited 36 participants across the treatment and control conditions, with n = 18 in each arm.

An *a priori* power analysis was conducted using G*Power [36]. With α = .05 (two-tailed), the proposed sample (*N* = 36) would detect moderate effects between groups (d = .50) with over 95% power using a repeated measures F test. A total sample of 16 participants would be needed to detect large effects (d = .8) with over 95% power using a repeated measures F test. For the regression analyses, a sample of 36 participants (α = .05) with three predictors would detect large effects (f^2^ = .35) with a power calculation of 80.95%, while six predictors would detect large effects with a power of 65.58%. The current sample was deemed appropriate as regression models with power less than 50% are deemed unreliable [37].

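### In its usual form the named MANOVA drops any woman with an incomplete outcome set, although 20% attrition is expected; a mixed model for each primary outcome would use the scores already collected

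*Protocol article*

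**What the plan says.** Under Quantitative analysis, the article fixes the between-group method: "Multivariate analysis of variance (MANOVA) will be used to examine differences in the primary and secondary outcome measures", comparing the intervention and matched control groups. Baseline scores enter as a covariate. A separate regression is limited to coping strategies and pain knowledge as dependent variables. The process evaluation looks at within-group change in the primary outcomes at each assessment.

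Under Sample size and power calculation, the starting point is a feasibility study: "This study proposed a total sample of 30 to be allocated across two conditions". The authors then "allowed for 20% attrition, thus we recruited 36 participants across the treatment and control conditions, with n = 18 in each arm". The power figures that follow are computed on the full 36.

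Table 1 gives the schedule for the primary outcomes. Pain Knowledge and Pain Coping Scenarios are measured at T1 to T5, and Pain Coping Strategies at T1, T4 and T5 only. Parents supply some outcomes as well: "Secondary outcome measures were administered to parents/guardians at T1, T4 and T5".

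The section on predictor variables reports that pre- and post-intervention data collection is complete and that analysis is under way.

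**The concern.** The authors expect one woman in five to be lost, yet name a method that in its ordinary form discards every case with a gap in the outcome vector or the covariate. Two of the three primary outcomes are measured five times, so a woman who leaves late may have three or four usable scores on each.

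Two things are at stake. The first is information: 36 is already small, and complete-case deletion makes it smaller. The second is bias. Recruiting 36 rather than 30 protects the sample size but does nothing about selective loss. Only the intervention arm attends twelve weekly sessions, so the reasons for loss may differ between arms in a comparison that is already non-randomised.

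**Working it through.** **1. The plan's own sample size.** Inputs from the sample size section: target 30, attrition 20%, recruited 36.
- 30 × 1.2 = 36, which reproduces the stated figure. Dividing instead gives 30 / 0.8 = 37.5, or 38.
- After 20% loss: 36 × 0.8 = 28.8, about 29 women, or 14 to 15 per arm.

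**2. Which scores are set aside.** From Table 1:

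| Woman lost | Knowledge, Coping Scenarios | Coping Strategies |
|---|---|---|
| after T3 | T1, T2, T3 exist | only T1 exists |
| after T4 | T1 to T4 exist | T1 and T4 exist |

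If T4 and T5 are outcomes in one MANOVA, neither woman contributes to the group comparison. If each time point has its own MANOVA, the woman lost after T4 stays in the T4 comparison but adds nothing at T5, and the woman lost after T3 is in neither. A mixed model uses every score in the table.

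**3. If parent forms share the model.** Assume that a share p of parent forms is returned at each of T1, T4 and T5, independently. Complete cases = 28.8 × p³.
- p = 0.95: 24.7
- p = 0.90: 21.0
- p = 0.80: 14.7

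The article gives no return rate, and these figures apply only to a single joint model.

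**4. Cost in power.** For the regression, use the noncentral F distribution with λ = f²N, degrees of freedom k and N − k − 1, f² = 0.35 and α = 0.05.
- N = 36: 80.95% with three predictors and 65.58% with six. Both stated figures are reproduced.
- N = 29: 69.4% and 51.6%.
- N = 28, six predictors: 49.4%, just under the 50% below which the article calls a regression model unreliable.

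These apply only if the regression loses the same women.

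For the group comparison the article claims that 36 "would detect moderate effects between groups (d = .50) with over 95% power using a repeated measures F test". It gives no correlation between repeated measures. Take ρ = 0.5 (assumed), f = d/2 = 0.25 and the group-by-time test with λ = f²Nm/(1 − ρ), where m is the number of time points.
- m = 5: 97.6% at N = 36, 93.4% at N = 29.
- m = 3: 90.6% at N = 36, 82.7% at N = 29.

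**5. Possible bias.** This is an illustration; every input is assumed. Scores have an exchangeable correlation of 0.5. Each arm loses 20%. Loss is random among controls; in the intervention arm it is more likely after poor T1 to T3 change (logistic slopes 1, 2 and 4). Large-sample simulation with 400,000 per arm gives these baseline-adjusted complete-case effects:
- true d = 0.50: 0.537, 0.555, 0.579
- true d = 0: 0.036, 0.060, 0.078

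The overstatement is therefore about 0.04 to 0.08 SD. Repeat runs agree to within about 0.01. An analysis that also uses the T3 score recovers the truth to within about 0.005. In this set-up the unadjusted difference is essentially unbiased; the distortion comes with baseline adjustment, which is what the plan specifies.

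**6. Scale.** With 14.4 women per arm and r = 0.5, the standard error of the adjusted effect is √(2/14.4) × √(1 − 0.5²) = 0.373 × 0.866 = 0.32 SD. The bias is then 0.04/0.32 to 0.08/0.32, about one eighth to one quarter of a standard error.

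**The case against.** The strongest reply is that the article never says only complete cases are analysed. It states no analysis set and no imputation or deletion rule, and a condensed article commonly leaves these to the full protocol or analysis plan. That stands: silence is no fault here, and imputation may be planned elsewhere. It does not remove the point, which concerns a method the article names and which needs such a supplement to suit the attrition the article expects.

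Three stronger readings are tempting, and the text does not support them.
- **One unreturned parent form removes a woman.** This requires self and parent ratings to enter a single joint MANOVA. The article does not say so. With separate models by outcome family, a missing parent form leaves the primary outcomes untouched.
- **Results come only from women who stayed with the programme.** Nothing ties the analysis to attendance. The aim's wording, "Participation in the menstrual pain management group results in an increase in participants’ ratings of pain coping strategies", is ordinary language for an objective and does not define a population. A woman can stop sessions and still be assessed, controls have no programme to leave, and the article says that delivery in the school timetable ensured consistent attendance. Any selection would be on completed assessments.
- **T2 and T3 scores go unused.** They feed the within-group process evaluation, from which later leavers are not excluded. They are absent only from the between-group comparison.

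It is also fair that the bias is small for a non-randomised pilot and rests on an assumed one-arm dropout pattern. Finally, recovery through T3 cannot work for Pain Coping Strategies, which has no T2 or T3 score.

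**Conclusion.** The point holds as a poorly matched choice of method. With 20% attrition expected, MANOVA in its usual form would leave about 29 of 36 women and set aside usable primary-outcome scores in the group comparison. That figure needs only the article's own attrition allowance and the usual behaviour of MANOVA without imputation. Larger losses (about 15 to 25 women left) depend on assumed parent return rates and a joint model. The bias of roughly 0.04 to 0.08 SD depends on outcome-related loss in one arm and on baseline adjustment; it is an order of magnitude, not a prediction. A reader might infer that the plan prescribes a completers-only analysis; it does not.

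**What to change.** Replace the MANOVA with a separate linear mixed model for repeated measures for each primary outcome, using all available scores from all 36 women by assigned condition:
- Pain Knowledge and Pain Coping Scenarios: T1 to T5.
- Pain Coping Strategies: T1, T4 and T5.

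Model parent ratings separately, so that a missing parent form cannot affect a participant's primary outcome. No further assessments are asked for, since pre- and post-intervention data collection is complete.

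The cost is a change of wording in the analysis plan and modest extra modelling. The estimate may be slightly smaller once incomplete cases count. For Pain Coping Strategies the gain is limited to women who have T4 but not T5, or the reverse; a woman lost before T4 contributes only her baseline there. The model relies on loss being explained by the observed scores, and it recovers part, not all, of the lost information.

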### Treatment allocation and matching process

#### Intervention condition

Due to the logistics and practicalities of delivering an intervention group to individuals within a wide geographical sampling area, a non-randomised process was used to assign participants to the intervention group.

A list was compiled of all females attending a special class for students with a mild or moderate intellectual disability or a school for students with mild or moderate intellectual disabilities, who receive support services from the Brothers of Charity Services within County Galway. The Principals of five schools were contacted, informed of the research study and invited to participate in the study. Two schools agreed to participate and were assigned to the intervention group. Parents/Guardians of the relevant students were then contacted and asked for their consent for their daughters to participate. Once consent was granted, assent was obtained directly from the young women.

This treatment allocation methodology allowed for the delivery of the intervention during the school day, at the location where the young women received their day service. This minimised inconvenience and school absence for research participants. This approach also enabled the intervention to be delivered to participants at an appropriate space within the school timetable e.g. during Social, Personal and Health Education (SPHE) class and so ensured consistent attendance.

The same approach was used to recruit participants attending Adult Day Centres providing educational and training opportunities to young women with mild and moderate intellectual disabilities, who receive support services from the Brothers of Charity Services within County Galway.

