#### Control condition

Individuals in the control condition were an equivalent comparison group matched by gender, age range and level of intellectual disability. These individuals were invited to participate in the study and were informed that they were allocated to the control condition and what that meant. They were informed that they would be offered the intervention condition, once the study was completed.

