## Discussion

In this study, we evaluated the impact on pain coping and pain management knowledge, of a menstrual pain management programme for young women with intellectual disabilities. We expected participants in the intervention group to report the use of a greater number of coping strategies and have greater knowledge of pain management strategies at both T4 and T5, compared to control group participants.

The content of the menstrual pain management programme was adapted from the theory-based cognitive behavioural therapy programme “Feeling Better – A manual for carers working with people who have intellectual disabilities and chronic pain” [20]. The programme that was developed reflected the input from the parents/guardians of research participants, on both content and delivery methods. The PRP qualitative component ensured that the theory-based programme was specifically tailored to meet the needs of this population. As stakeholders, parents/guardians have insights into the training needs of their daughters and the possible challenges in delivering such a programme. Caregivers control access to medical/health services [3,38], so it is very important that they are involved with health interventions for those who are in their care.

A significant advantage to this study was the inclusion of process evaluation to determine which elements of a cognitive behavioural therapy programme work best for individuals with intellectual disabilities. Hunter [39] identified the need for clarification on effective components of CBT approaches for pre-menstrual symptoms and this is particularly relevant for this population. Moderator analyses of the outcome of the intervention will enable a better understanding of who this type of training is most effective with and under what conditions. Such information will enable us to optimize treatment for each individual into the future. For this reason, a number of variables which are assumed to be related to pain coping were measured in this study.

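### The only stated between-group test mixes primary with secondary outcomes, and age and degree of disability are not fixed in it although sites were allocated by agreement

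*Protocol article*

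**What the plan says.** Under Quantitative analysis, the between-group comparison is given in one sentence: "Multivariate analysis of variance (MANOVA) will be used to examine differences in the primary and secondary outcome measures between the intervention and matched control groups". No separate between-group test of the primary outcomes is named. The Measures section names pain coping and pain management knowledge as primary, measured by three questionnaires. Its text then counts four secondary measures: severity, interference, self-efficacy and catastrophizing. Table 1 lists only two measures as secondary and puts self-efficacy and catastrophizing under process variables.

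On adjustment, the same paragraph says "Baseline scores will be included as a covariate to allow for regression to the mean and a multiple regression model will be used", then "A step-wise method of regression analysis will be conducted with predictors entered using the backward method", and describes this as exploratory model building. The dependent variables of the regression are the primary outcomes. Its covariates are introduced by "Predictors will include the demographic characteristics of age and degree of intellectual disability as well as time since onset of menstruation", followed by other menstrual, symptom, treatment and medication variables. Group and site are not named among them.

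On allocation, the Intervention condition section says "Two schools agreed to participate and were assigned to the intervention group" and reports that adult day centres were recruited in the same way. The Control condition section describes the controls as "an equivalent comparison group matched by gender, age range and level of intellectual disability".

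**The concern.** There are two linked problems.

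First, the omnibus hypothesis is not the trial's question. A MANOVA rejects when the groups differ on any combination of the outcomes entered. The Secondary outcome measures section itself says that pain intensity is not what the programme chiefly targets, and the catastrophizing scale records parents' thoughts. A difference on such measures could make the test significant with coping and knowledge unchanged.

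Second, the intervention arm consists of sites that chose to take part, so the groups may differ beforehand. Age and degree of disability are obvious candidates and both are recorded. As written, they are handled by a procedure that may delete them and that does not name the group effect as a term. The article therefore fixes no adjusted estimate of the effect of the programme on the primary outcomes. The study calls itself a pilot, but its stated aim is to find out whether the programme is more effective than usual care.

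**Working it through.** **The plan's own power figures.** Sample size and power calculation states over 95% power for d = .50 with N = 36, using a repeated measures F test. Take f = d/2 = .25, two groups, and an assumed correlation of .5 between time points.

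- Group-by-time interaction, λ = f²·N·m/(1 − ρ): for m = 3, 4 and 5 time points λ = 13.5, 18.0 and 22.5, and power is 90.6%, 95.2% and 97.6%.
- Between-groups effect, λ = f²·N·m/(1 + (m − 1)ρ): λ = 3.375 for m = 3 and 3.75 for m = 5, and power is 43% and 47%.
- Regression, λ = .35 × 36 = 12.6: power is 80.95% with three predictors and 65.58% with six. Both reproduce exactly.

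So the stated 95% matches an interaction test with four or five time points. It does not describe a MANOVA across pooled outcomes.

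**What a significant pooled MANOVA can mean.** From the article: 18 per arm, α = .05, three primary questionnaires, and four secondary measures (Measures text) or two (Table 1). Assumed: no effect on any primary, d = .8 on each secondary, equal pairwise correlation r. For two groups the MANOVA is Hotelling's T². With p outcomes, of which q are affected:

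- D² = d²/(1 − r) × [q − r·q²/(1 + (p − 1)r)]
- λ = (18 × 18/36) × D² = 9D²
- F has p and 36 − p − 1 degrees of freedom

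| Outcomes (p) | Affected secondaries (q) | r | D² | λ | Rejection |
|---|---|---|---|---|---|
| 7 | 4 | 0 | 2.56 | 23.0 | 90% |
| 7 | 4 | .3 | 2.09 | 18.8 | 81% |
| 7 | 4 | .5 | 2.56 | 23.0 | 90% |
| 5 | 2 | 0 | 1.28 | 11.5 | 66% |
| 5 | 2 | .3 | 1.33 | 12.0 | 68% |
| 5 | 2 | .5 | 1.71 | 15.4 | 80% |

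If only one of four secondaries is affected, simulation gives 38% (r = .3) to 49% (r = .5). Under a complete null the test rejects at about 5%, as it should.

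**What adjustment does.** Assume a pre-existing difference of 0.5 SD, no treatment effect, and a pre-post correlation of .5 to .7. In simulation, the comparison without a baseline covariate is falsely positive 11% to 18% of the time. With the baseline score as covariate the rate is about 5% if the difference acts only through the measured baseline, and 8% to 13% if a stable group difference persists. Whether the MANOVA includes that covariate therefore matters, and the baseline score alone may not be enough.

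**Power of a separate test per primary.** With baseline correlation r, z = d/[√(1 − r²) × √(2/18)], and .5/√(2/18) = 1.50.

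- r = .5: z = 1.50/.866 = 1.73
- r = .7: z = 1.50/.714 = 2.10

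At α = .05 (critical value 1.960) normal-approximation power is 41% and 56%. At Holm's first step, α = .05/3 = .0167 (critical value 2.394), it is 25% and 38%.

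**The case against.** The case for the plan has substance.

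- *A reader might infer that the comparison is unadjusted for confounders.* The document does not support that. A baseline-score covariate is planned, controls were matched on age range and level of disability, and the Predictor variables section describes models in which moderators such as age interact with intervention condition. What stands is narrower. The covariate is not tied clearly to the MANOVA, and no matching tolerance is given. Gender matching does nothing in an all-female sample. Moderator models ask for whom the programme works and do not fix an adjusted primary effect. The regression's predictor list may not be exhaustive, but group is not on it.
- *A reader might infer one single MANOVA.* The number of models is not stated, and there could be one per time point or domain. Even so, primary and secondary outcomes are named together, and no test is reserved for the primaries.
- *The 81% to 90% scenario is extreme.* That is fair. It needs large effects on all four secondaries and none on the primaries. With Table 1's two secondaries the range is 66% to 80%, and with one affected measure of four it is lower still.
- *Baseline appears contradictory.* The sentence "Within-groups differences will be measured at each time-point, including baseline" might be read as clashing with the use of baseline as a covariate. The two statements can describe separate analyses, and the section later presents within-group change as process evaluation. No error is shown.
- *The coping score might seem to be a total count.* The Discussion says "We expected participants in the intervention group to report the use of a greater number of coping strategies", but that is an expectation and not an analysis definition. The Primary outcome measures section already codes wellness-focused strategies separately.
- *Multiplicity rules are commonly left to an analysis plan, and this is an exploratory pilot.* Both points lower the stakes. They do not change which outcomes the stated test combines.

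**Conclusion.** The point holds in a limited form. The only between-group test that the article states covers primary and secondary outcomes together, so its significance is not evidence about coping or knowledge. The 66% to 90% range shows how far the two can come apart, but it rests on assumed effects (d = .8 on every secondary, none on the primaries) and assumed correlations of 0 to .5, none of which are in the article.

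On confounding, the defect is the absence of a fixed adjusted estimate: allocation followed site agreement, while age and degree of disability are left to data-driven elimination and the place of the baseline covariate is unclear. Matching and the moderator models reduce the problem without removing it. The size of any actual bias cannot be known from the document. This should be changed, but in an exploratory pilot it does not undermine the study as a whole.

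**What to change.** Make the primary analysis a separate ANCOVA at T4 for each of the three primary questionnaires. Keep group, that measure's T1 score, age and degree of disability in every model, with no data-driven selection. Report the adjusted difference with a confidence interval. If significance is claimed, apply Holm across the three: three unadjusted tests would carry 1 − .95³ = 14.3% familywise error under independence. Treat T5 as a maintenance analysis and analyse the secondary measures separately. Settle which measures are secondary, since the Measures text and Table 1 differ. Keep the backward regression as exploratory, and state that confounding by site remains.

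No new data are needed. Age and degree of disability cost two degrees of freedom per model. Holm, if used, lowers first-step power for d = .50 from about 41%–56% to 25%–38% (baseline correlation .5 to .7 assumed), which is a further reason to lead with estimates and intervals. The article says that pre- and post-intervention data collection is complete and analysis is under way, so the change should be dated and reported as made at that stage.

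### The regression's power is given for three and six predictors, but the listed model has about eleven terms; it falls below the plan's own 50% limit, at full size or after the allowed attrition

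*Protocol article*

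**What the plan says.** Under Sample size and power calculation, the protocol article states that "we recruited 36 participants across the treatment and control conditions, with n = 18 in each arm", after allowing for 20% attrition. For the regressions, at alpha 0.05 and a large effect (f² = 0.35), it gives 80.95% power with three predictors and 65.58% with six. It then calls the sample appropriate on the ground that "regression models with power less than 50% are deemed unreliable".

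Under Quantitative analysis, the dependent variables of the regression are coping strategies and pain knowledge, which are the primary outcomes. Baseline scores enter as a covariate. On selection: "A step-wise method of regression analysis will be conducted with predictors entered using the backward method". On validation: "This method will be used for exploratory model building and will be cross-validated by then randomly splitting the data". On candidates: "Predictors will include the demographic characteristics of age and degree of intellectual disability as well as time since onset of menstruation". The list goes on to how often and how long the participant menstruates, the number of symptoms and how often they occur, and three further items: medical history, treatment and medication use. No removal threshold and no split fraction are given. Treatment group is not listed among the predictors of this regression. The Predictor variables section does say that moderators were interacted with the intervention condition.

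**The concern.** The sample size section sets a limit for a usable regression and shows that models with three and six predictors meet it. The analysis section describes a larger model. Backward elimination starts from the full list, so the full count is what the limit should be applied to. If the described model falls below 50% power, the plan calls its own analysis unreliable.

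The selection and validation steps add to the problem. Data-driven selection from many candidates in 36 people can keep predictors by chance, and splitting so small a sample leaves too few people either to build the model or to test it. The results matter beyond this pilot: the Discussion expects moderator findings to show whom the programme suits and to guide how treatment is tailored later.

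**Working it through.** **Inputs from the article.** N = 36; alpha = 0.05; f² = 0.35; attrition 20%, so 36 × 0.8 = 28.8, about 29 completers; limit 50% power.

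**Counting terms.** One by one: age, level of disability and time since onset (3); frequency and duration of menstruation (2); number and frequency of symptoms (2); history, treatment and medication use (3). That is 3 + 2 + 2 + 3 = 10. The baseline score makes 11, and group, if entered, makes 12. Taken as blocks, the list is age, disability, time since onset, menstrual pattern, symptoms and medical background: 6, or 7 with baseline and 8 with group as well.

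**Formula.** Overall F test of a multiple regression with k terms: df₁ = k, df₂ = N − k − 1, noncentrality λ = f² × N. Power is the probability that a noncentral F(k, N − k − 1, λ) exceeds the 5% critical value of the central F.

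**Reproducing the plan.** λ = 0.35 × 36 = 12.6. With k = 3 (df 3, 32) power is 80.95%; with k = 6 (df 6, 29) it is 65.58%. Both match exactly, so this is the calculation the plan used.

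**Applying it to the listed model** (at N = 29, λ = 0.35 × 29 = 10.15):

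| Terms | N = 36 | N = 29 |
|---|---|---|
| 6 (blocks only) | 65.6% | 51.6% |
| 7 (blocks + baseline) | 61.1% | 47.0% |
| 8 (blocks + baseline + group) | 57.0% | 42.8% |
| 9 | 53.1% | 39.1% |
| 10 (one by one) | 49.5% | 35.7% |
| 11 (+ baseline) | 46.1% | 32.6% |
| 12 (+ baseline + group) | 43.0% | 29.8% |

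At N = 36 the limit is crossed between 9 and 10 terms; at N = 29, between 6 and 7.

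**The split.** The fraction is not stated, so these are assumptions:
- Halves of 18: λ = 0.35 × 18 = 6.3, giving 42.4% for 3 predictors, 26.0% for 6 and 14.7% for 10.
- An 80% training part (about 29): 51.6% for 6 and 35.7% for 10, with 36 − 29 = 7 people left for testing.

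**Selection.** This was checked by simulation: ten independent normal candidates, baseline and group forced in, 1,500 runs per setting. The removal thresholds of 0.05 and 0.10 are assumptions.
- No true predictor, N = 36: at least one candidate is kept in about 44% of runs (threshold 0.05) or 67% (0.10). At N = 18 the figures are about 51% and 75%. Correlating the predictors at 0.3 changed these little.
- One to three true predictors with joint f² = 0.35: chance predictors are 27–57% of those kept at N = 36 and 53–77% at N = 18.

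**The case against.** **The count.** The list is punctuated in a way that permits six blocks, which matches the six-predictor power figure. On that reading the full-sample model clears the limit (61.1% with baseline, 57.0% with group as well), and even at exactly ten predictors the shortfall is half a point (49.5%). This stands as far as it goes: failure at full sample size depends on how the predictors are coded. It does not rescue the plan, because the same section puts the baseline score in the model, and seven terms with 29 completers have 47.0%.

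**The power measure.** The overall F test loses power as terms are added. A test of a single coefficient whose own partial f² is 0.35 would keep about 93% at N = 36 whether there are 3 terms or 12. That is true, but the plan chose the overall test and attached its 50% limit to it.

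**The label.** The regression is called exploratory, the study is a pilot, and the group comparison is assigned to MANOVA. This lowers the seriousness. It does not remove the conflict, since the 50% limit is applied to these very regressions without exception.

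A reader might also infer three stronger things that are not supported:
- That the sample is cut in half. The article says only that the data are split at random, so every figure for 18 people is conditional on that assumption.
- That the model will return mostly chance predictors. At N = 36 with the plan's assumed effect they were a minority of those kept in most settings tried; often is supported, mostly is not.
- That selection will drop the treatment term. Group is not listed as a predictor in this regression. In any case, a plain two-group test with d = 0.5 and 18 per arm has 30.8% power at 0.05 and 43.2% at 0.10. It therefore misses in 57–69% of cases with no selection at all, about the same as the 57–68% seen under backward elimination.

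**Conclusion.** The concern holds in a limited form. The stated power figures are correct for three and six predictors but do not cover the model described. Counted one by one with baseline, the model has 46.1% power at 36 participants (43.0% if group is entered) and 32.6% with about 29 completers. On the lenient count of seven terms it has 61.1%, falling to 47.0% after the allowed attrition. The plan's own limit is therefore missed at full size on the plain count, and after attrition on both counts.

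Backward elimination at this size is unstable and often keeps chance predictors. A random split leaves too few people to validate the model under either fraction examined. These results rest on f² = 0.35 and the overall F test, both taken from the plan, and on assumed removal thresholds and split fractions. Because the analysis is exploratory and the group comparison does not rest on it, this is a point that should be fixed rather than one that must be.

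**What to change.** For each primary outcome, fit one pre-stated model on all participants with treatment group, baseline score and one or two baseline predictors (for example level of intellectual disability and age), all forced in. Drop backward elimination. Replace the random split with bootstrap optimism correction or leave-one-out validation on the full sample. Report the remaining background variables one at a time, labelled hypothesis-generating.

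Restate the power for the model actually fitted. On the same formula, three terms have 80.95% at N = 36 and 69.4% at N = 29; four terms have 75.5% and 62.7%. All are above the plan's limit.

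The cost is some wording and a few lines of code, with no new data. The article says that analysis is in progress, so the model should be fixed and dated before these regressions are run. The drawback is that fewer predictors are examined formally.
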